### Interventions

All participants will receive health education recommended by the guidelines of Osteoarthritis Research Society International (OARSI) [30]. On the basis of health education, the group A will receive the placebo intra-articular injection; the group B will receive the PRP intra-articular injection; the group C will receive TC and placebo intra-articular injection; the group D will receive TC and PRP intra-articular injection. During 12-week intervention, intra-articular injection of PRP and placebo will be performed under ultrasound guidance. The frequency and dose of intra-articular injection will be consistent between the placebo and PRP in the four groups. Injection will be performed once a week, three consecutive times as a course, after a week of rest to continue the next course, a total of 3 courses (12 week). Additionally, the TC interventions in the Group C and D will be carried out 3 days per week for a total of 12 weeks.

### Health education

The efficacy of health education for treat KOA have been demonstrated by the organizations of OARSI and Osteoarthritis and Musculoskeletal Diseases (ESCEO) [30]. Thus, we will use health education as basis intervention. The health education will include two parts: (1) an educational booklet and a video will be provided to the patients to accomplish the home-based self-learning; (2) weekly group meeting with face to face. The topics covered by health education include: osteoarthritis, aging, how to exercise for the elderly, the effect of TC on health, and the education and management of KOA pathogenesis factors, etc.

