### Inclusion criteria

The inclusion criteria will be as follows: (1) meet the diagnostic criteria for KOA; (2) aged 50–75 years; (3) Kellgren–Lawrence (KL) grade I to III based on radiographic classification; (4) without the experience of TC; (5) volunteer to take part in the study and sign the informed consent form.

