### Randomization, allocation concealment and blinding

The stratified randomization with gender and KL grade as factors will be used to randomly assign the eligible participants to four groups. First, the participants will be grouped by gender. Then, male and female will be grouped by KL grade. After grouping, there will be six subgroups: (1) male, KL = I; (2) male, KL = II; (3) male, KL = III; (4) female, KL = I; (5) female, KL = II; (6) female, KL = III. For any one subgroup, the participants will randomly divide into group A, B, C and D group, and all group A, B, C and D group are merged to form a new group A, B, C and D group. The randomization number lists will be generated by the random number generator of the SPSS software (Version 22.0; IBM Corp., NY, USA).

The allocation of participants will be hidden in opaque numbered and sequentially sealed envelopes, prepared by a researcher who did not participate in the recruitment and assignment of the groups. The corresponding envelopes will be opened to determine a patient’s group assignment once the participants enrolled have completed all baseline assessments. In addition, physiotherapists with same level, TC coaches and IAI operators also will be followed randomization and randomly assigned to any group.

Due to the visible nature of the exercise intervention, blinding of the study investigators and the participants for TC will be impossible [28]. To ensure blinding of the PRP and concealment of randomization, the independent laboratory pharmacist prepared a syringe with PRP and a syringe with placebo (isotonic saline: 0.9% sodium chloride) [29]. They covered study syringes with a specially manufactured thick plastic covering sheath to conceal the appearance of the study intervention. After the intra-articular injection, the syringe covered by the sheath (containing either the remnants of the PRP or saline) will be handed back to the independent research assistant, who disposed of the syringe in effort to maintain blinding of the study team. The success of blinding will be assessed by asking patients just after the injections what treatment they thought they had received. Furthermore, blinding will be applied to the outcome assessors and statisticians who conduct the final statistical analyses in this protocol to avoid potential detection bias. The outcome assessors will be responsible for data collection and analysis, and they will not be involved in the subject recruitment process.

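### The health education given to all four arms covers the health effects of Tai Chi, an avoidable contamination risk for D vs B and B vs C

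*Protocol article*

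**What the plan says.** The Interventions section makes education the base for every arm: "All participants will receive health education recommended by the guidelines of Osteoarthritis Research Society International (OARSI"). The Health education section describes two parts. The first is home material: "an educational booklet and a video will be provided to the patients to accomplish the home-based self-learning". The second is a "weekly group meeting with face to face". One list of topics serves both parts, and it includes "how to exercise for the elderly, the effect of TC on health, and the education and management of KOA pathogenesis factors".

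Tai Chi itself is assigned to two arms only: "the TC interventions in the Group C and D will be carried out 3 days per week for a total of 12 weeks". Every participant must enter "without the experience of TC" (Inclusion criteria). The section on randomization and blinding states that "blinding of the study investigators and the participants for TC will be impossible".

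The Tai Chi section describes a short, modified form that is easy to learn and can be practised at any time and place. It also provides video clips for home learning to each participant. The section heading suggests that groups C and D are meant, but the words do not limit it to them.

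The aims at the end of the Background name D vs B, D vs C, B vs C and B vs A.

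**The concern.** The Tai Chi comparisons depend on groups A and B not practising Tai Chi. A common package that covers its health effects works against that, particularly for a therapy that the article says is easy to take up without supervision. The Background describes Tai Chi as effective and safe in knee osteoarthritis, so the topic will presumably be presented as a benefit.

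The main consequence is uptake in the arms not assigned Tai Chi, over 12 weeks and the follow-up to 12 months. This bears on Aim 1 (through D vs B) and Aim 2 (B vs C). None of the listed outcomes would show afterwards how much uptake there had been.

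A lesser consequence is expectation. The article does not call the WOMAC self-reported, but pain, stiffness and daily function rest on what the patient says, and the anchor question for the MCID is a patient rating. Patients who know that they were not given Tai Chi, and are then taught its value, may score themselves worse. This would inflate the Tai Chi effect, whereas uptake shrinks it in D vs B.

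**Working it through.** **The plan's own figure.** The Sample size section gives 168 evaluable participants and a 20% drop-out allowance: 168/0.8 = 210, or 52.5 per arm, rounded up to 53, and 4 x 53 = 212. This step reproduces. Drop-out is the only allowance made. The 168 comes from a four-group repeated-measures ANOVA with effect size 0.25, not from a pairwise Tai Chi contrast, and nothing below depends on it.

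**Assumed inputs.** c is the share of group B that takes up Tai Chi. The documents give no value, so 10%, 20% and 30% are shown. Those who take it up are assumed to gain the full effect of the trial programme, which makes each figure an upper bound for its c.

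**D vs B.** Count improvement as positive. A group B patient who takes up Tai Chi with full effect has the expected outcome of group D.

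- Mean of B with uptake = (1 - c) x B + c x D
- D minus that mean = (1 - c) x (D - B)
- Sample size for fixed power varies with 1/effect^2, so it is multiplied by 1/(1 - c)^2

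| c | Effect retained | Sample size multiplier |
|---|---|---|
| 10% | 0.90 | 1/0.81 = 1.23 |
| 20% | 0.80 | 1/0.64 = 1.56 |
| 30% | 0.70 | 1/0.49 = 2.04 |

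As an illustration, assume a true Tai Chi effect of 0.5 SD, 42 evaluable per arm (168/4) and an unadjusted two-sided 5% test. Power for D vs B is 63% with no uptake, and 54%, 45% and 36% at the three values of c.

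**B vs C.** This sets PRP against Tai Chi, so the formula above does not apply. With additive effects, C minus B without uptake is TC - PRP. With uptake it is TC - (PRP + c x TC) = (1 - c) x TC - PRP.

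Take assumed effects of 0.5 SD for Tai Chi and 0.3 SD for PRP, with c = 20%:

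- Without uptake: 0.5 - 0.3 = 0.2
- With uptake: 0.8 x 0.5 - 0.3 = 0.1

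The difference halves, although c is only 20%. If the two effects were equal, a true difference of zero would become one in favour of B. If PRP were the stronger, the gap would widen. In every case the result moves towards B.

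**B vs A and D vs C.** Each pair shares its assigned Tai Chi status and receives the same education, so neither is directly distorted.

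**The case against.** Education common to all arms is a legitimate background treatment, and general exercise advice given equally to everyone is not contamination. That stands, and only the Tai Chi topic is at issue.

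The topic concerns the effect of Tai Chi on health, not how to perform it. The trial programme is three 60-minute sessions a week under an experienced master, and self-started practice would probably achieve less. That stands too, and is why the multipliers are upper bounds.

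Most of the expectation bias would exist without this topic. Patients cannot be blinded to Tai Chi, the limitations paragraph of the Discussion says so, and Recruitment and enrollment has everyone told the study's purpose, method and potential benefits. This also stands: the topic may add somewhat to that bias, and removing it would not remove the bias.

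A reader might infer four stronger points that the article does not support:

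- **That A and B hear about Tai Chi every week.** The meetings are weekly, but Tai Chi is one topic in an open list and no frequency is given for it.
- **That C and D patients pass Tai Chi on at the meetings.** Nothing says that arms meet together, and an article may leave such arrangements to the full protocol.
- **That 53 per arm must be multiplied by these factors.** They belong to a pairwise D vs B contrast. Uptake in A and B weakens only the Tai Chi part of the four-group effect.
- **That the Tai Chi-naive criterion was set to keep A and B clean.** No reason for it is stated.

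The core is untouched. The article itself lists the health effects of the experimental treatment among the topics taught to its comparator arms, so this is stated content and not a missing detail.

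**Conclusion.** The point holds as an avoidable contamination risk, not as a demonstrated bias. It concerns D vs B and B vs C. In D vs B, full-effect uptake of 10%, 20% or 30% in group B would raise the sample size for that contrast by at most 1.23, 1.56 or 2.04 times. In B vs C it would shift the result towards B by c times the Tai Chi effect, if effects are additive. The uptake share is assumed throughout. Because any added expectation effect could oppose the dilution in D vs B, the net direction there cannot be stated in advance, and without a record of Tai Chi practice it could not be worked out later. The change is worth making because it costs little, not because the expected damage is known to be large.

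**What to change.** - Take the Tai Chi topic out of the common booklet, video and meetings, and teach it only within the Tai Chi sessions of groups C and D. General exercise advice can stay in the common package.
- State in the Tai Chi section that the video clips and written material go to groups C and D only.
- Add a case report form item on Tai Chi practice for all arms at T2, T3, T4 and T5. Report uptake by arm and use it in a sensitivity analysis of D vs B and B vs C.

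The cost is one edited education module, one clarifying sentence and one form item. The small downside is that education content will then differ slightly between arms.

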### PRP preparation and injection

The fresh venous blood samples of the participants will be collected via venipuncture, which underwent the process of two-step differential centrifugation in order to obtain PRP [1, 31]. One syringe of 36 mL of autologous blood will be collected from the median cubital vein, and inject into four 9-mL extraction tubes. Among four extraction tubes, three tubes containing 3.8% trisodium citrate as anticoagulant, and the remaining one contains nothing, which will be used for hematological analysis. After blood collection, the tubes will be submitted to double centrifugation (Smart Prep III, Harvest Technologies Corp, USA). Blood samples will be centrifuged for 10 min at 1800 rpm to separate the erythrocyte layer. The upper plasma layer will be carefully collected in a new sterile propylene tube while attempting to not remove the leukocyte layer. The plasma from all tubes will be centrifuged again for 12 min at 3400 rpm to obtain a two-part plasma, with the upper part consisting of platelet-poor plasma and the lower part consisting of LP-PRP. After discarding platelet-poor plasma, about 5 mL of LP-PRP will eventually be obtained. The product monograph reported that an 1 mL of LP-PRP prepared this method with approximately 1244 × 10^6^ platelets and 24.7 × 10^6^ white blood cells [32]. Finally, approximately 6220 × 10^6^ platelets will be injected into the knee of the patients with KOA under ultrasound guidance.

The patient will be instructed to remain in a supine position, and the knee joint will be slightly flexed. The outer and upper part of the patella of the affected knee will be taken as the injection point, where routine disinfection will be performed and a sterile towel will be spread. A 21-gauge needle will be inserted into the knee joint at the upper outer quadrant of the patella under ultrasonographic guidance, and 5 mL PRP will be injected into the joint cavity after the relevant joint fluid was pumped back. After the injection, patients will be advised to avoid heavy or repetitive stress to the knee joint for 48 h. Patients will be instructed to avoid co-interventions and nonsteroidal anti-inflammatory drugs (NSAIDs) 24 h prior to the intervention [33].

### Tai Chi

The Tai Chi program is mainly based on a nine-form Yang-style, which is a brief and modified version of 64-form Yang-style [34, 35]. It can be easily learned and practiced without restrictions on time and space. More importantly, it is suitable for the patients with KOA, because some movement patterns with high knee joint load are modified by the Tai Chi master to accommodate KOA symptoms and help limit dropouts. The patients will participate in three 60-min Tai Chi sessions conducted weekly for 12 weeks. Each session includes: (1) warm up and review of Tai Chi principles and techniques, 10 min; (2) Tai Chi exercises, 40 min; (3) cool-down relaxation, 10 min. The teaching is carried out by a Tai Chi master who has over 10 years’ experience conducting Tai Chi exercise. Information about the principles and skillsets of each form of TC, and Video clips will be provided to each participant for home learning.

### Outcome measures

Outcome measures will be assessed by profession rehabilitation assessor, biochemical analyst and ultrasound doctor at baseline (T1) before intervention, 6 weeks (T2) and 12 weeks (T3) during intervention, and 3 months (T4) and 12 months (T5) during follow-up period. The demographic and clinical characteristics of the all participants will be collected at the time of enrollment.

### Primary outcomes

Efficacy: The Western Ontario and McMaster Universities Osteoarthritis Index (WOMAC) will be used to evaluate the score of the pain, stiffness and daily functional activities of the participants. A number of studies demonstrated that the WOMAC is a reliable and valid instrument for evaluating the joint function of KOA [36, 37]. The aggregate score of the WOMAC is 96, which mainly includes pain (20 points), stiffness (8 points) and daily functional activities (68 points). The higher the score is, the more serious the knee joint dysfunction is. In addition, the anchor-based method will be utilized to determine the minimal clinically important difference (MCID) in order to evaluate the clinical significance of the changes in WOMAC [38]. All patients will be asked to rate their knee improvement compared to baseline at 3 and 12 months. The question will be: “How is your health today compared with baseline?” Patients will be able to choose from five Likert response options: “a great deal better,” “somewhat better,” “equal,” “somewhat worse,” and “a great deal worse.” The MCID will be determined by calculating the average change score for patients who reported their knee improvement as “somewhat better” in the transitional question. This will involve subtracting the baseline scores from the scores at 3 and 12 months during the follow-up period. The MCID proportion (MCID%) will be calculated as the percentage of the sample with a change in scores that surpasses the MCID threshold.Acceptability: The acceptability is an important part of the evaluation of intervention. The rate of referral, retention and drop-out will be used to comprehensively evaluate the acceptability of interventions. • Referral rate is defined as the ratio of the number of referrals made by different departments and hospitals to all participants (T1); • Retention rate is the ratio of the number of participants who completed the study (T5) to all participants (T1); • Drop-out rate is the ratio of the number of participants who dropped out after randomization to all participants (T1), talk with the drop-out participants to identify their reasons for dropping out.Safety: The occur rate of adverse events is defined as the ratio of the number of occurred participants to all participants (T1), which will be used to evaluate the safety of intervention. During the intervention and follow-up, the adverse events (e.g., pain, fall) will be recorded on the Case Report Form (CRF) by the way of the monitor and self-report, and will be evaluated for relevance to the intervention.

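### The MCID anchor is described as a knee rating, but the transition question quoted in the plan asks about general health

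*Protocol article*

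**What the plan says.** All of the relevant text is in the protocol article, Primary outcomes, under Efficacy.

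- **What is to be rated:** "All patients will be asked to rate their knee improvement compared to baseline at 3 and 12 months".
- **The item as printed:** "How is your health today compared with baseline", with five answers running from much better to much worse.
- **How the MCID is derived:** it is the "average change score for patients who reported their knee improvement as “somewhat better” in the transitional question".
- **How change is computed:** "This will involve subtracting the baseline scores from the scores at 3 and 12 months during the follow-up period".
- **Direction and range of the scale:** "The higher the score is, the more serious the knee joint dysfunction is", and "The aggregate score of the WOMAC is 96".
- **The responder measure (MCID%):** the "percentage of the sample with a change in scores that surpasses the MCID threshold".

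The article presents the MCID as an addition to the WOMAC score, used to judge the clinical significance of WOMAC changes.

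**The concern.** The description before the item and the derivation after it both name the knee. The item between them names only health. These are different constructs, and the plan itself separates them: SF-36 is a secondary outcome covering broad physical and emotional health, while WOMAC covers the knee.

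The item matters because it selects the patients whose mean WOMAC change becomes the threshold. Participants are 50 to 75 years old and are asked at 3 and 12 months, so general health can move for reasons unrelated to the knee. The exclusion criteria limit such changes but cannot remove them. Tai Chi is unblinded whole-body exercise, and the health education given to every group covers its effect on health. A patient could therefore feel healthier with little change in the knee.

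The article states no other criterion for clinical relevance. The sample size rests on a standardised effect size of 0.25, not on a WOMAC difference. If the anchor is weakened, the reading of the WOMAC result as clinically important or not is weakened with it.

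**Working it through.** The plan states no MCID and no responder percentage, so there is no figure to reproduce. The check has three parts.

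**1. The texts side by side.** The introductory sentence says knee, the printed item says health, and the derivation sentence says knee. Following the printed item does not deliver what the other two sentences describe. This needs no arithmetic.

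**2. What a weaker anchor does to the threshold.** Every input here is an assumption, because the document gives none:

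- WOMAC improvement is normal with mean 10 and SD 15.
- The 'somewhat better' group lies between the 50th and 85th percentiles of the anchor, so it holds 35% of patients.
- The anchor correlates with WOMAC improvement at *r*.

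The mean standardised anchor score in that band is the difference of the normal densities at its limits, divided by its share: (0.399 − 0.233) / 0.35, about 0.473.

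Threshold = mean + *r* × SD × 0.473. The percentage beyond it is the normal tail above the threshold.

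| *r* | Threshold | Beyond threshold |
|---|---|---|
| 0.6 | 10 + 0.6 × 15 × 0.473 = 14.3 | 39% |
| 0.3 | 10 + 0.3 × 15 × 0.473 = 12.1 | 44% |

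As *r* approaches 0, the threshold tends to the overall mean of 10 and the percentage to 50%.

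A simulation on different assumptions behaves the same way. It used a mean change of −12, an SD of 15, and 'somewhat better' as the 45th to 80th percentile of the anchor. When the correlation fell from 1.0 to 0.2, the MCID moved from −17.0 to −13.0 and the percentage improving beyond it from 37% to 47%.

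In both examples the 'somewhat better' group sits on the improved side of the overall mean, so a weaker anchor lowers the bar. If that group sat on the other side of the mean, the same pull would raise it. The direction in this trial therefore cannot be fixed from the document either.

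**3. Whether the sign convention adds an error.** Higher WOMAC is worse and change is follow-up minus baseline, so improvement is negative: a fall from 50 to 38 gives 38 − 50 = −12. The MCID is the mean of these same signed changes, so threshold and individual changes share one convention.

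Take an assumed mean change of −12, SD 15 and MCID −10. The proportion improving by more than the MCID is P(change < −10) = Φ((−10 + 12)/15) = 55.3%. With the subtraction reversed, the mean is 12 and the threshold 10, and P(change > 10) is again 55.3%. The sign convention does not alter the result.

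**The case against.** **The intended construct is clear, and the questionnaire is not shown.** Two sentences say knee. The case report form may name it too, and the printed item may be a loose rendering. This is fair, and it means one cannot conclude that patients will answer the wrong question, or that data beyond repair will be collected. It does not remove the contradiction: the article prints the item in quotation marks, so this is more than a detail lost in condensing.

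**The effect is small and the main analysis is untouched.** This largely stands. The illustrated shift is 14.3 − 12.1 = 2.2 points on a 96-point scale. One threshold applied to all arms also leaves the contrast between arms almost unchanged. With assumed arm means of 7.5 and 12.5 and SD 15, the responder rates are 32.5% and 45.2% at a threshold of 14.3 (difference 12.7 percentage points), and 37.9% and 51.1% at 12.1 (difference 13.1 after rounding). A reader might infer that the threshold would stop separating responders. These numbers do not show that.

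**The sign.** A reader might also infer that, because improvement is negative, the responder percentage will come out as its complement. That requires reading a change that surpasses the MCID as one numerically greater than a negative threshold, which would count unchanged and worsened patients as having reached a benefit. The threshold comes from patients who said they were better, so the natural reading is improvement beyond it, and that gives the correct percentage. What is left is that the direction of the inequality is not written out.

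**Conclusion.** The point holds for the anchor. The plan contradicts itself on what patients are asked. If the printed question is used, changes in general health unrelated to the knee can misclassify the 'somewhat better' group, pull the WOMAC MCID toward the overall mean change and shift the responder percentage.

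The contradiction rests on the text alone. The size does not: 14.3 against 12.1 points and 39% against 44% depend wholly on the assumed mean, SD, percentile band and correlations, and indicate a modest shift. The comparison of WOMAC scores between groups is unaffected. What depends on this item is the statement of whether those differences matter to patients.

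The document does not support the further claim that subtracting baseline from follow-up makes the percentage wrong.

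**What to change.** Before the item is used, reword it to name the treated knee, for example: *How is your knee today compared with before treatment?* The cost is one questionnaire line. If the case report form already names the knee, only the published wording needs correcting.

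As a clarification only, add one clause saying that a responder is a patient whose WOMAC improvement is at least as large as the MCID. The follow-up-minus-baseline convention can stay.

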**Methods:**

This study protocol will be a placebo-controlled, assessor-blinded randomized trial involving 12-week intervention and 1-year follow-up. The stratified randomization will be used to randomly assign the 212 participants to four groups: group A (placebo IAI); group B (PRP IAI); group C (TC and placebo IAI); group D (TC and PRP IAI). Injection will be performed once a week, three consecutive times as a course, after a week of rest to continue the next course, a total of 3 courses (12 week). Additionally, the TC interventions will be carried out 3 days per week for a total of 12 weeks. The primary outcome measures will include the efficacy (Western Ontario and McMaster Universities Osteoarthritis Index), acceptability and safety of these interventions. The secondary outcome measures will include physical function (Timed Up and Go test), walking function (Gait Analysis), inflammatory factor levels (e.g., Interleukin-1 β, interleukin-6, vascular endothelial growth factor), quality of life (36-Item Short Form Health Survey), volume of patellofemoral cartilage and effusion-synovitis (MRI). Two-way of variance with repeated measures will be applied to examine the main effects of the group and the time factor and group-time interaction effects for all outcome measures.

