### Recruitment and enrollment

Two hundred and twelve participants with KOA will be recruited from the Shanghai Seventh People’s Hospital and neighboring communities, through the ways of flyers, posters, recommended by rehabilitation therapist or neurologist, and WeChat official account. We will communicate with potential participants with participation intention by telephone for the first step of screening and asked them to self-report whether they met the inclusion criteria. For the subjects who passed the first step of telephone screening, he or she will be invited to face-to-face examination and evaluation, and to fully determine that the participants meet the inclusion criteria and not meet the exclusion criteria. In addition, we will inform the purpose, method and potential benefits of the present study to all participants, as well as the principle of voluntary participation. All patients who met the inclusion criteria and agreement to participate will be required to provide their written informed consent.

Recruitment will start from February 1, 2024, until when 212 participants are enrolled.

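### Acceptability, a primary outcome, rests on a referral rate fixed before allocation and on two overlapping retention measures, leaving one weak, indirect measure of whether the interventions are acceptable

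*Protocol article*

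**What the plan says.** The Methods part of the abstract lists the primary outcomes as efficacy on the WOMAC, together with "acceptability and safety of these interventions". The section Primary outcomes states how acceptability will be measured: "The rate of referral, retention and drop-out will be used to comprehensively evaluate the acceptability of interventions". It then defines the three rates:

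- Referral: "Referral rate is defined as the ratio of the number of referrals made by different departments and hospitals to all participants (T1").
- Retention: "Retention rate is the ratio of the number of participants who completed the study (T5) to all participants (T1").
- Drop-out: "Drop-out rate is the ratio of the number of participants who dropped out after randomization to all participants (T1"). To this the protocol adds an instruction to "talk with the drop-out participants to identify their reasons for dropping out".

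Under Outcome measures, T1 is the baseline assessment before intervention, and the last two visits are "3 months (T4) and 12 months (T5) during follow-up period". The section on randomisation has the envelopes opened only after all baseline assessments are complete. Participants are to be found "through the ways of flyers, posters, recommended by rehabilitation therapist or neurologist, and WeChat official account" (Recruitment and enrollment). The Statistical analysis section plans a chi-square or Fisher test across the four groups for categorical variables.

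**The concern.** A primary outcome described as the acceptability of the interventions should respond to the interventions. One of its three components cannot, because it is settled before anyone knows which group a participant will join. The other two appear to count the same event from opposite sides, over a period that runs well past the end of treatment.

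At stake is one of the three named primary conclusions. The Discussion closes by saying that the results will demonstrate acceptability of the combined treatment, and the abstract favours Tai Chi partly for its good adherence. Yet no component uses the number of injections received or classes attended. Under the retention definition, a participant who stops Tai Chi in week 2 but attends every assessment counts as retained. One who completes all treatment but misses the 12-month visit counts against acceptability.

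**Working it through.** **1. Referral.** The order of events is referral or self-presentation, screening, consent, T1 assessments, envelope opened, treatment. Referral status is therefore a pre-allocation characteristic. Under randomisation its expected difference between any two groups is zero, whatever PRP or Tai Chi does. Taken over the whole trial, it shows what share of recruitment came through departments and hospitals rather than the other listed routes.

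**2. Retention and drop-out.** In a group of N participants at T1, let C be the number completing T5 and D the number counted as drop-outs. Let x be those counted in both (for example, stopped treatment but attended T5) and y those counted in neither (missed T5 but not labelled drop-outs). Then C + D = N + x − y, so

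retention + drop-out = 1 + (x − y)/N.

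If everyone who misses T5 is a drop-out and nobody else is, x = y = 0 and retention = 1 − drop-out. With 53 per group, each participant in x or y shifts the sum by 1/53, or 1.9 percentage points. The protocol does not define x or y, so the identity is conditional.

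When it holds, the two rates give the same test. Take an assumed 11/53 against 17/53 drop-outs, so 42/53 against 36/53 retained:

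chi-square = 106 × (11 × 36 − 17 × 42)² / (53 × 53 × 28 × 78) = 106 × 318² / 6,134,856 = 1.747, p = 0.186,

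for drop-out and for retention alike.

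**3. Window.** Treatment lasts 12 weeks. Taking 12 months as 52 weeks, treatment fills 12/52 = 23% of the time to T5 if the 12 months run from baseline. If they run from the end of treatment, the share is 12/(12 + 52) = 19%. Most of the period over which a participant can be lost therefore lies after treatment.

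**4. What drop-out could still show.** The plan's own allowance reproduces: 168/4 = 42 per group, 42/(1 − 0.20) = 52.5, rounded up to 53, and 4 × 53 = 212. A 20% drop-out is thus 53 × 0.20 = 10.6 participants per group. Pairwise power at two-sided 0.05, with p̄ the mean of the two rates, is

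power = Φ{ [|p1 − p2| − 1.96·√(2p̄(1 − p̄)/53)] / √([p1(1 − p1) + p2(1 − p2)]/53) }.

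The comparison rates are assumptions, because the protocol gives only the 20% allowance:

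| Drop-out, two groups | Calculation | Power |
|---|---|---|
| 20% vs 30% | (0.100 − 0.165)/0.0836 = −0.78 | 0.22 |
| 20% vs 35% | (0.150 − 0.170)/0.0855 = −0.23 | 0.41 |
| 20% vs 40% | (0.200 − 0.174)/0.0869 = 0.29 | 0.62 |

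The planned Bonferroni adjustment lowers these further.

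**5. Treatment exposure not used.** The Interventions section gives 3 injections per course × 3 courses = 9 injections, and 3 Tai Chi sessions per week × 12 weeks = 36 sessions. Neither count enters any of the three rates.

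**The case against.** The strongest reply is that drop-out is a legitimate measure. It is counted from randomisation, so its window includes the whole treatment period. It can differ by group, a four-group categorical test is already planned, and participants who leave will be asked why. All of this stands. A reader might infer that the outcome cannot show anything about the acceptability of PRP or Tai Chi, and the documents do not support that.

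Other stronger readings also fail:

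- **That retention and drop-out are exactly the same number.** Drop-out is not defined. If it covers leaving the assigned intervention, the participant who quits Tai Chi but attends T5 is both retained and a drop-out, and the two rates separate.
- **That the referral rate is not a proportion and can exceed 1, or that most participants will come by flyer or WeChat.** The first requires counting referrals of people who never enrol, which the wording does not settle. For the second, the protocol lists routes but gives no numbers. Even read as the share of enrolled participants who were referred, the rate is still only a recruitment source.
- **That attendance will not be recorded.** This is a condensed article, and such records may be described elsewhere. The point is narrower: the acceptability definition, given here in full, does not use them.

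It can also be said that the Discussion links acceptability with feasibility, where a trial-level referral figure has a place. That supports reporting referral, but not as a measure of whether an intervention is acceptable. Finally, acceptability is not named in the three aims and does not drive the sample size, which limits the consequences.

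**Conclusion.** The point holds in limited form. Of the three components, referral carries no information about any intervention. This follows from the order of events and needs no numerical assumption. Retention and drop-out amount to essentially one measure, exactly so only if missing T5 and dropping out are the same event. That measure mixes abandoning a 12-week treatment with missing visits up to the 12-month follow-up. It is informative but indirect, with pairwise power of roughly 0.2 to 0.6 for assumed differences of 10 to 20 percentage points.

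The definitions are stated in full and chosen badly, so this is not detail left to another document. It should be corrected because acceptability is declared primary. The WOMAC comparison is unaffected.

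**What to change.** - Move the referral rate and 12-month retention to the reporting of trial conduct.
- Define drop-out so that stopping the assigned intervention and leaving the study are separate events. Report each by arm, with the reasons the protocol already plans to collect.
- Add treatment adherence by arm to the acceptability outcome: the proportion of the 9 scheduled injections received in all groups, and the proportion of the 36 Tai Chi sessions attended in groups C and D.

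This changes no injection or exercise schedule. The cost is an attendance log at the injection clinic and the Tai Chi class, if none is kept, and a reworded definition. The log needs to start with the first participant, since attendance is hard to reconstruct later. Adherence is itself only a proxy: a participant may attend and dislike the treatment, or miss sessions for unrelated reasons. It should therefore be read together with the stated reasons for stopping.
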